### Sample size

An a priori sample size calculation was conducted using the eta-partial square value of the group-by-time interaction for worst knee pain (0.19) obtained in a previous study that compared the effects of three gait retraining programs on runners with patellofemoral pain [27]. In G*Power software [28], we used ANOVA: repeated measures, within-between interaction, with the following parameters: effect size f = 0.48 (obtained through eta-partial square value); level of confidence = 0.05; power = 99%; number of groups = 3; number of measurements = 3. The total sample size obtained was 21 participants, however, to account for losses during the follow-up period, the final sample size will be 30 participants.

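### The 99% power claimed for 21 participants puts a partial eta squared on the wrong effect-size scale; the same 0.19 gives about 56% power at 21 and about 78% at 30

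*Protocol article*

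**What the plan says.** The Sample size section of the protocol article starts from the "eta-partial square value of the group-by-time interaction for worst knee pain (0.19"), taken from an earlier three-program gait retraining study. It converts this to Cohen's f and uses the G*Power procedure "ANOVA: repeated measures, within-between interaction", with the inputs "effect size f = 0.48 (obtained through eta-partial square value); level of confidence = 0.05; power = 99" per cent and "number of groups = 3; number of measurements = 3". The result is given as follows: "The total sample size obtained was 21 participants, however, to account for losses during the follow-up period, the final sample size will be 30 participants".

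The section does not name the effect-size option used in the software, the correlation assumed between visits or any nonsphericity correction. Under Data analysis, the planned test is a mixed ANOVA of three groups by three time points, with Sidak-adjusted pairwise comparisons.

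**The concern.** A total of 21 people, seven per arm, is very few for 99% power in a three-arm trial when the interaction explains 19% of the relevant variance. The likely cause is a known trap. The software's default option for this procedure expects an f defined on the between-person scale, and then adds the benefit of repeated measurement through the number of visits and their correlation. A partial eta squared reported from a repeated-measures ANOVA is defined differently: it is the interaction sum of squares divided by itself plus the within-subject error. It already contains that benefit.

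The sample size rests on this one calculation. The Introduction expects each program to do better than control and neither program to be superior to the other. If readers believe power is 99%, a non-significant result in either comparison invites the conclusion that there is no difference, although the trial may well have missed the effect it was planned around.

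**Working it through.** **Inputs from the Sample size section.** Partial eta squared 0.19; f = 0.48; alpha 0.05; k = 3 groups; m = 3 measurements; N = 21, raised to 30. **Assumed, because not stated:** sphericity (epsilon = 1) and, for the reproduction only, a between-visit correlation rho = 0.5, the software default.

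**Step 1: the conversion.** f = sqrt(0.19 / (1 − 0.19)) = sqrt(0.2346) = 0.484. The stated 0.48 is correct.

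**Step 2: reproducing 21.** The interaction F test has df1 = (k − 1)(m − 1) = 4 and df2 = (N − k)(m − 1) = 2(N − 3). On the default scale the noncentrality is lambda = f² × N × m / (1 − rho).

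- N = 21: lambda = 0.48² × 21 × 3 / 0.5 = 29.03; power 99.04%.
- N = 20: power 98.6%.

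So 21 is exactly the smallest N that reaches 99%. Other correlations on this scale give a different N: 29 at rho = 0.3, 25 at 0.4 and 18 at 0.6.

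**Step 3: what that lambda implies.** With df2 = 36, a lambda of 29.03 corresponds to a partial eta squared of 29.03 / (29.03 + 36) = 0.45. If N(m − 1) = 42 is used in place of df2, it is 29.03 / (29.03 + 42) = 0.41. Either value is more than twice the 0.19 that was assumed.

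**Step 4: power on the matching scale.** With f² = partial eta squared / (1 − partial eta squared), the noncentrality is lambda = f² × df2 = f² × 2(N − 3), with no further division by (1 − rho). A more generous convention is lambda = f² × N × (m − 1).

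| Completers | lambda = f² × 2(N − 3) | Power | Power, generous convention |
|---|---|---|---|
| 21 | 0.2304 × 36 = 8.29 | 56% | 63% |
| 24 | 0.2304 × 42 = 9.68 | 64% | 71% |
| 27 | 0.2304 × 48 = 11.06 | 72% | 77% |
| 30 | 0.2304 × 54 = 12.44 | 78% | 83% |

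With unrounded f = 0.4843, the first power column becomes 57% at 21 and 79% at 30. In multiples of three, 80% power needs 33 completers (30 under the generous convention). For 99% power the figure is 57 to 63, depending on the convention and the rounding of f. If epsilon is 0.75 instead of 1, the 56% and 78% fall to about 47% and 68%.

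**Step 5: a check without power software.** Suppose a trial with 21 completers observes exactly 0.19. Then F(4, 36) = (0.19 / 0.81) × 36 / 4 = 2.11, p = 0.10, below the 5% critical value of 2.63. A design in which the assumed effect, observed exactly, is not significant cannot have 99% power to detect it.

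**Step 6: pairwise comparisons.** All of the above concerns the omnibus interaction. For one pairwise contrast with Sidak adjustment over three comparisons, the per-comparison alpha is 1 − 0.95^(1/3) = 0.017. The difference detectable with 80% power is then 1.97 SD at 7 per arm and 1.57 SD at 10 per arm in a two-sample t test. With the error pooled over three arms it is 1.88 and 1.53 SD. The SD is that of whatever quantity is compared, for example the change from baseline.

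**The case against.** Several points can fairly be made for the plan.

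- **The software option is inferred.** The article names neither the effect-size option nor the correlation, so the mechanism is a deduction. It is a strong one, since the default settings give exactly 21. The conclusion does not depend on it either: neither partial-eta-squared convention gives more than about 64% at 21, and Step 5 uses no software option.
- **The source study is not at hand.** Its number of visits and its model cannot be checked, so the corrected power is conditional on 0.19 being an ordinary repeated-measures partial eta squared from a comparable design. This caveat stands. It qualifies the 56% and 78%, but it does not support the 99%.
- **Thirty will be enrolled.** Twenty-one is reached only if 9 of 30 (30%) are lost. With all 30 retained, the check in Step 5 gives F(4, 54) = 3.17, p = 0.02, and power is 78% to 83%. This also stands, and the restated text should show both ends. But the article presents the extra nine only as cover for losses, so 21 is the number to which the 99% is attached.
- **Sizing on the omnibus test matches the planned analysis.** It does, and the lack of a pairwise calculation is not an error in itself. The detectable difference is a useful addition because the hypotheses are stated pairwise; it is secondary to the scale error.

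**Conclusion.** The stated power is wrong. An effect of 0.19 on the partial-eta-squared scale does not give 99% power with 21 participants; it gives 56% to 64%, depending on the convention and the rounding of f. With all 30 retained it gives 78% to 83%. Under the first convention in Step 4 the trial would miss its own assumed effect about 44% of the time with 21 completers and about 22% of the time with 30. The figures rest on sphericity and on the 0.19 being a conventional repeated-measures value. A violation of sphericity lowers them further. The error lies in the central design figure and is large, so it should be corrected before the results are interpreted.

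**What to change.** Rerun the calculation with the software's partial-eta-squared (SPSS-type) effect-size option and replace the 99% statement. The revised text should:

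1. Keep 30 enrolled, and report about 56% power with 21 completers and about 78% with all 30 for the omnibus interaction at f = 0.48 and alpha 0.05.
2. Name the effect-size option and the sphericity assumption, and state the correlation between visits wherever one is used.
3. Give the difference detectable with 80% power for each program against control, saying which SD it refers to and whether the error is pooled over the three arms.
4. Drop the 99% claim, so that a non-significant result is not read as strong evidence of no effect.

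The cost is a less favourable stated figure. Enrolment, design and analysis need not change. If the sponsor wants to keep 99% as a target, the consequence is roughly 57 to 63 completers.

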### Randomisation/Blinding

Participants will be randomized into experimental or control groups with an allocation ratio of 1:1:1 by means of block randomization (block size of 2x15) performed with the aid of a sequence of numbers generated on a computer. The allocation will be hidden by means of opaque envelopes, sealed and numbered consecutively. A laboratory employee who will not participate in the evaluations and interventions will generate the allocation sequence, hide the allocation and allocate participants for interventions. Due to the nature of the intervention, both the participants and the researcher responsible for the gait retraining cannot be blind to the allocation of interventions; however they will be strongly warned not to confide the allocation in subsequent evaluations and instructed to perform the retraining sessions alone. In this way, the risk of the blinded-assessor and other participants knowing what retraining is being performed is diminished. Also, the main researcher who will conduct data analysis will be blinded to assigned group.

### Data collection

Pain will be assessed using the Visual Analog Pain Scale [29], which consists of a numerical scale from 0 to 10 points, where 0 means no pain and 10 means the maximum pain ever experienced. Pain during daily activities (usual) and running will be measured. VAS is a reliable and valid scale for patients with PFP [30]. Function will be assessed using the Patellofemoral Disorders Scale [31], which contains 13 questions that assess the severity of symptoms and limitations in different activities related to PFP. It presents a score between 0 to 100 points where the lower the score the worse the function. The Patellofemoral Disorders Scale is a reliable and valid scale for patients with PFP, which has been translated into Portuguese [30,31]. The kinematics of the lower limbs will be assessed through digital videos using two webcams (MyoVideo 139 HD Color Webcam) sampling at 30 frames per second and two leds (LED Floodlight) [32]. Reflective markers will be placed on the manubrium sterni and bilateral on the anterior superior iliac spine (ASIS), greater trochanter, lateral femoral epicondyle, fibular head and lateral malleolus [33]. All participants will be instructed to run at 10–12 km/hour on a motorized treadmill (Movement XL 1600). A treadmill acclimatization period of 6 min will be used before running kinematics are measured [34]. The frontal plane camera will be placed on a portable tripod perpendicular to the frontal plane at a height of 1.30m and a distance of 2.55m from the treadmill. The sagittal plane camera will be placed on a portable tripod, perpendicular to the sagittal plane at a height of 1.15m and a distance of 2.50m from the treadmill. The video recordings will be analyzed using the software MyoResearch 3.14—MyoVideo (Noraxon U.S.A. Inc.). In the frontal plane the angles assessed will be: contralateral pelvic drop; hip adduction [33,35,36]. These angles will be evaluated during midstance. In the sagittal plane the angles assessed will be: foot inclination; tibia inclination; ankle dorsiflexion; knee flexion [33,37,38]. Foot and tibia inclination will be evaluated during initial contact while ankle dorsiflexion and knee flexion during midstance. In the frontal plane, the deepest landing position (near midstance) will be determined visually by slowly advancing the video frame by frame [33,37,38]. Since the cameras are synchronized this position will also be used to determine the midstance in the sagittal plane. Initial contact will be determined visually by slowly advancing the video frame by frame, and will be defined as the first time that the foot touched the ground [37]. To analyze the proposed angles, seven steps will be considered [33]. The study of Dingenen and colleagues [39] has found excellent inter-rater reliability (ICC) for all angles with ICC’s ranging from 0.93 to 0.99.

### Rehabilitation programs (independent variables)

Each runner will take part in one of the three groups, two partially supervised gait retraining groups, one with a focus on impact (Group A), the other with a focus on cadence (Group B), and a control group (Group C). Before starting the intervention, participants will run with their regular shoes at a speed of 10/12 km/hour [40], in order to verify the usual values of the acceleration of tibia and cadence. After this assessment, it is possible to establish the threshold of impact and cadence that will be used in the programs. Both parameters will be acquired with the accelerometer Tgforce (v2.0.0.10) [20,41]. Also, these parameters will be collected immediately and six-months after the protocol to see how the participants have adapted to the proposed running-pattern. In groups A and B, the protocol will be performed four times a week, with a gradual duration from 15 to 30 minutes, over two weeks. There will be two supervised (first and fifth session) and six unsupervised sessions. In the final 4 training sessions the feedback will be gradually removed (Table 1). We chose a faded feedback design since it prevents the dependency on external feedback, promotes the development of response accuracy and consistency (important components of skill learning) and produce long-term retention [42]. In addition, participants will be instructed to run with this new running-pattern during the next six months.

**Table 1 pone.0250965.t001:** Protocol performed in groups A and B.

Week	Day	Training	Time of feedback	Time of training
1	1	Supervised	15 minutes	15 minutes
	2	Unsupervised	18 minutes	18 minutes
	3	Unsupervised	21 minutes	21 minutes
	4	Unsupervised	24 minutes	24 minutes
2	5	Supervised	21 minutes	27 minutes
	6	Unsupervised	15 minutes	30 minutes
	7	Unsupervised	9 minutes	30 minutes
	8	Unsupervised	3 minutes	30 minutes

Source: Authors.

Group A participants will receive visual feedback (acceleration of the tibia captured using an accelerometer) and verbal feedback (commands given by the clinician) throughout the intervention period. The accelerometer Tgforce (v2.0.0.10) will be taped to the anteromedial aspect of the subject’s distal tibia [20]. The study of Pairot de Fontenay and colleagues [41] assessed the concurrent validity of popular, commercially available wearable sensors in estimating vertical ground reaction force during running, and found that the Tgforce was the only wearable sensor to be valid in estimating instantaneous vertical loading rate. A screen positioned in front of the treadmill will show a graph of the acceleration of the tibia in real time captured by the accelerometer. On the screen, the participant will see a line that represents approximately 50% of the average peak tibial acceleration obtained during the last minute of running [19,20]. Subjects will be instructed to “run softer,” “make their footfalls quieter”, and to keep the acceleration peaks below the line [20,21,43]. Group B participants, on the other hand, will receive guidance regarding their cadence and will run with the help of a metronome with an adjusted cadence increased by 7.5 to 10% [44–46]. In both groups, the clinician will provide instructions repeatedly during the first minute, and provide positive or negative reinforcement approximately every 30 seconds for the rest of feedback period [43]. Participants will be instructed to maintain the new running pattern during the other unsupervised sessions held at a location of their choice [22]. Group C participants will not receive any retraining strategies or guidance until the study ends. After the 24-week follow-up, participants will receive guidance relevant to their condition based on biomechanical assessments previously performed.

Regarding the participants’ adherence, to ensure that they carry out the protocols and that they are executed properly, the supervised session will be carried out first. Other measures adopted by the researchers will be: (I) guidance after the supervised session on how the unsupervised sessions should take place; (II) give a copy of Table 1 containing information’s regarding the program and showing how unsupervised sessions should take place; (III): daily text message on the participants’ phone advising them on how the sessions should take place; (IV) inform the participants that they can contact the researchers to answer questions about the protocol.

Participants will be allowed to continue performing running activities during the study. There will be no need for the presence of a data monitoring committee or interim analyses and audits in order to determine the continuation or end of the study as the time for executing the protocol/study is short and the risks offered by it are minimal. The monitoring of possible adverse events will be done daily during the protocol period, any participant who reports pain worsening or other musculoskeletal pain will be instructed to reduce their training volume. The adverse effects will be addressed descriptively in the study results. If the pain persists to the point where participation is impossible, the participant will be considered as a drop-out of the intervention because of injury and the previous data collected will be used in the analysis.

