## Introduction

Millions of people practice running, an activity that requires minimal equipment and benefits cardiac, metabolic, and mental health. However, running tends to cause high injury rates (19% to 92%) leading to social and economic losses [1–5]. In runners, the knee is the main site affected (7.2% to 50%) [5] and one of the main injuries is patellofemoral pain (PFP) (5.5%) [6]. Unfortunately, 55% of treated individuals present unfavourable recovery at three months and 40% at twelve months [7]. Also, 57% do not recover completely in five to eight years [8].

Various interventions are recommended for the treatment of individuals with PFP, among which gait retraining can be highlighted [9]. A systematic review by Agresta and Brown [10], demonstrated immediate and short-term effects (1 and 3 months) on pain, function, and biomechanics of individuals with PFP, results corroborated by Barton and colleagues [11], who associated current evidence with expert opinions. Findings were also outlined by critical reviews conducted by Jeon and Thomas [12] and Davis and colleagues [13].

However, the evidence of the benefits of gait retraining comes mainly from case series and quasi-experimental studies that did not have a control group and did not report adverse effects or limiting factors for this intervention [10–12]. The need for high-quality evidence justifies conducting clinical trials that show the effects of gait retraining programs in individuals with PFP.

The systematic review and meta-analysis of Neal and colleagues [14], found moderate evidence that runners with PFP had increased hip adduction and contralateral pelvic drop, based on cross-sectional studies. Reducing peak knee flexion could also be an important variable to address in runners with PFP, given that greater flexion has been associated with greater patellofemoral joint loading [15]. Increasing running cadence has been shown to be effective in reducing hip adduction [16,17], contralateral pelvic drop [16], and knee flexion [16,17] in subjects with PFP. Three additional studies show that increasing cadence reduces compression forces in the patellofemoral joint [15,18,19]. Another strategy with interesting results is modifying knee joint loading through visual and verbal feedback on impact. Indeed, two studies found reductions in ground reaction force loading rates using specific cues on “run softer” and an accelerometer [20,21], and this has been shown to reduce the incidence of PFP [22].

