### Outcomes measures (dependent variables)

The primary outcome of the study will be: (I) pain during daily activities (usual)—assessed using the Visual Analog Pain Scale [29]; The secondary outcomes will be: (II) pain during running—assessed using the Visual Analog Pain Scale [29]; (III) function—assessed using the Patellofemoral Disorders Scale [31]; (IV) kinematics of the lower limbs in the frontal (contralateral pelvic drop; hip adduction) [33,35,36] and sagittal planes (foot inclination; tibia inclination; ankle dorsiflexion; knee flexion) [33,37,38]–assessed through digital videos using two webcams (MyoVideo 139 HD Color Webcam) sampling at 30 frames per second and two leds (LED Floodlight) [33]. The video recordings will be analyzed using the MyoResearch 3.14 –MyoVideo software (Noraxon U.S.A. Inc.). The kinematic variables of interest were chosen based on previous studies [14,15,19,47,48]. The systematic review and meta-analysis of Neal and colleagues [14] shows a relationship between increased hip adduction and contralateral pelvic drop with PFP. The study of Wille and colleagues [47] showed that foot inclination angle and peak of knee flexion are variables that may predict knee joint loading and PFJ forces during running. Tibia inclination during initial contact is related with cadence and length [48] and these are associated with PFJ forces [18,19]. For the comparison of the three study subgroups, the average of points on the visual analog scale of pain, average of points on the scale of Patellofemoral disorders and the peak in degrees of the contralateral pelvic drop, hip adduction, knee flexion and ankle dorsiflexion during midstance and foot inclination and tibia inclination during the initial contact will be considered. The three groups will be compared before (t0), immediately after (t2) and six months (t24) after starting the protocol.

Regarding the retention of the participants, to ensure that there are minimal losses during the follow-up period, the researchers will make a monthly phone call to monitor pain, the current level of training, physical activity practice and if the participants sought for other methods of treatment. Participants can withdraw from the study for any reason at any time, in which case the researchers will collect the pain and function outcomes using the aforementioned instruments (if possible) and report the reasons why these patients did not complete the follow-up (Fig 1).

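### Adverse event monitoring is stated only for the two-week program, although the retraining groups are told to keep the new gait for six months

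*Protocol article*

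**What the plan says.** All references are to the protocol article.

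- **Monitoring window** (Rehabilitation programs, adherence and safety paragraphs): "The monitoring of possible adverse events will be done daily during the protocol period". Worsening pain and other musculoskeletal pain are named there as reportable problems. Adverse effects are to be described in the results, with no period or arm specified.
- **Length of the program** (Rehabilitation programs): for groups A and B, "the protocol will be performed four times a week, with a gradual duration from 15 to 30 minutes, over two weeks". Tibial acceleration and cadence are measured again after it: "these parameters will be collected immediately and six-months after the protocol".
- **Continued use of the new gait** (Rehabilitation programs): "participants will be instructed to run with this new running-pattern during the next six months".
- **Assessment times** (Outcomes measures): "The three groups will be compared before (t0), immediately after (t2) and six months (t24) after starting the protocol".
- **Contact during follow-up** (Outcomes measures, introduced as a way to limit losses): "the researchers will make a monthly phone call to monitor pain, the current level of training, physical activity practice", and whether other treatment was sought. For participants who withdraw, the team will "report the reasons why these patients did not complete the follow-up".

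**The concern.** The instruction to run differently lasts far longer than the stated surveillance for harm. A changed running pattern may cause trouble at sites other than the study knee, and the article allows for this by naming other musculoskeletal pain alongside worsening knee pain. After week 2 it names no means of collecting such events.

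This matters more than usual here for two reasons. The Introduction justifies the trial partly because earlier gait retraining studies "did not report adverse effects or limiting factors for this intervention". The hypothesis also claims that benefit lasts to six months. As written, a six-month benefit statement would stand beside a harm record that is secured for two weeks only. No data monitoring committee is planned, so the descriptive harms report is the main safety information that the trial will produce.

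**Working it through.** **Step 1: what the protocol period means.** Under Rehabilitation programs the protocol is eight sessions over two weeks, and measurements are taken six months after it. Under Outcomes measures, t24 is counted from its start. In both places the protocol is the short program, not the whole study. One phrase in the paragraph on data monitoring couples protocol and study, and could suggest a longer period. On that reading, however, adverse events would be checked daily for 24 weeks, which fits poorly with follow-up contact that is only monthly. Two weeks is the natural reading.

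**Step 2: share of follow-up outside the window.** The document gives no such share, so there is no figure of its own to reproduce. The formula is (follow-up weeks − 2) / follow-up weeks.

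- If six months run from the start of the program (t24): (24 − 2)/24 = 22/24 = 91.7%.
- If 24 weeks are counted from the end of the two-week program: (26 − 2)/26 = 24/26 = 92.3%.

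Both round to 92%.

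**Step 3: what the 92% measures.** It is calendar time. The table of sessions prescribes 15 + 18 + 21 + 24 + 27 + 30 + 30 + 30 = 195 minutes of training in the program. The article gives no running volume after week 2, so a share of running exposure cannot be computed.

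**Step 4: what the later contacts would catch.**

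| Source after week 2 | Would probably catch | Could miss |
|---|---|---|
| Monthly call | Knee pain, a drop in training, treatment sought | A new injury elsewhere, if the runner is not asked about it; nothing links the answers to adverse event recording |
| Reasons for not completing follow-up | Injuries that end participation | A runner who is hurt, cuts back and stays in the trial |
| t24 assessment | Usual pain, running pain, function | Injuries that arose and resolved before t24; new sites |

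If calls come about every 30 days, 22 weeks (154 days) contain about 154/30 ≈ 5 of them, against daily monitoring in the first two weeks.

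**Step 5: the control group.** Group C follows no program, so the article does not say what the window means for it, even in weeks 0–2.

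**The case against.** The strongest reply is that the article ties only *daily* monitoring to the program and then promises, without a time limit, to describe adverse effects. Monthly calls do monitor pain, and the text does not confine that to the knee. A new running injury would often show up as pain, reduced training or treatment sought, and withdrawals are explained. Call scripts and event forms normally sit in a full protocol, and this article refers to supplementary files that are not shown.

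Much of this stands, and it rules out three stronger readings that a reader might infer:

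- *Injuries after week 2 are not counted as harms.* No sentence excludes them, and the calls and withdrawal reasons would pick up some.
- *92% of the exposure is unmonitored.* The figure is calendar time, and group C has no exposure to a new gait at all.
- *Retraining will look safer than it is relative to control.* No between-arm test of harms is planned. Controls may also keep running, and a gap after week 2 affects all arms. A bias in favour of retraining would need more late injuries in groups A and B than in C, and the article gives no basis for assuming that.

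The reply does not remove the mismatch itself. The article states a window, and that window is shorter than the period for which the new gait is prescribed. This is more than detail left to another document. The calls are presented as a retention measure, their listed content omits new injuries, and nothing says that they feed the adverse event report.

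**Conclusion.** The point holds as a mismatch between the stated monitoring window and the instructed use of the new gait. Explicit adverse event monitoring covers about 2 of 24 weeks. For the other 22 (about 92% of calendar follow-up), harms depend on a monthly retention call that was not set up to record them. Later musculoskeletal events are likely to be under-recorded; by how much cannot be said from the article.

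This rests on reading the protocol period as the two-week program, and on the calls containing no more than the article lists. If the full protocol already routes call answers into adverse event recording in all arms, only the wording needs correcting.

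The primary outcome, the efficacy analysis and the sample size are unaffected. With 30 participants in three equal arms (30/3 = 10 each), harm counts will be descriptive in any case. This is an inexpensive improvement and no threat to the trial's main conclusion.

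**What to change.** 1. State that adverse events are collected from randomisation to t24 in groups A, B and C.
2. Add one structured question on new or worsened musculoskeletal pain to the monthly calls already planned, worded identically in all three groups, and say that the answers enter the adverse event record. Identical wording matters because groups A and B have supervised sessions and group C does not.
3. Report events descriptively by arm, as number of events and number of participants affected, separately for weeks 0–2 and 2–24.

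No treatment rule changes. The cost is slightly longer calls and one extra table. The change is best made before follow-up begins, because events that are not recorded when they happen are hard to recover at t24.
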